### Trial Sample

This trial has been approved by Hammersmith and Queen Charlotte's & Chelsea Hospitals Research Ethics Committee, with site approval for Ravenscourt Park Hospital, St Mary's Hospital, St Thomas' Hospital, Royal Free Hospital, Heatherwood and Wexham Park Hospital, and Charing Cross Hospital.

Eligible patients include those currently on the waiting list for spinal surgery with either (a) signs, symptoms and radiological evidence of lateral nerve root compression, that is, patients presenting with radicular pain with an associated neurological deficit or with neurogenic claudication (pain in the buttock, thigh or leg that improves with rest), or (b) lumbar disc prolapse, that is, patients with root symptoms and signs and MRI confirmation of lumbar disc herniation. Patients with any of the following will be excluded from participation in the trial; any condition where either the intervention or the rehabilitation may have an adverse effect on the individual; previous spinal surgery; spinal surgery where a fusion procedure is planned due to the unknown hazards of the activity programme for this type of surgery; pregnant women; inadequate ability to complete the trial assessment forms; any patient who is unable to attend the rehabilitation or the reviews or who is unsuitable for rehabilitation classes.

Written informed consent will be obtained from all patients and baseline assessment completed prior to surgery and randomisation into the trial. Patients will be notified of their randomisation following surgery. Those allocated to either the booklet-only group or the rehabilitation-plus-booklet group, will get the "Your back operation" on discharge (see details below).

The trial aims to recruit 344 patients into the trial with 86 patients in each of the 4 sub-groups. This figure was based on being able to detect a 20% relative improvement in the Oswestry Disability Index (version 2.1). We anticipate a mean ODI of 40 in the control group and 32 in the exercise group at 1 year, to have a 90% chance of detecting a between-group difference of 8 points on the ODI and declaring it statistically significant using a two-sided alpha= 0.05, requires a total of 344 patients. This calculation assumes a standard deviation of 20 in each group and allows for loss to follow-up of 23%, as found in earlier descriptive work [20].

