### Proposed Analyses

Analyses will begin with a descriptive comparison of the trial groups before surgery to confirm that randomisation has produced groups that are balanced with respect to known confounders. This will include age, sex, type of surgery, ethnic background, marital status, body mass index, occupation type, work status and smoking status. Pre-operative scores on the primary and secondary outcomes will also be presented by group.

Full functional recovery from back surgery can be protracted, so the primary outcome of interest is the between-group difference in score on the ODI at one-year follow-up, based on intention-to-treat (modified to exclude patients recruited in error). Missing outcome data are expected because of this timeline. Multiple imputation under missing at random [64] will be used for patients with some follow-up but unmeasured one-year outcomes.

Groups will be compared via analysis of covariance, with adjustment for stratifying block using a linear mixed model. If assumptions appear violated, some transformation of the outcome will be taken such that assumptions appear sensible. If this fails, a non-parametric test will be used.

Parallel analyses will be performed for booklet vs. no-booklet and rehabilitation vs. no-rehabilitation, with the sample-size calculation given above applying to each of these. These calculations will be followed by an analysis which tests for an interaction of effect of the two interventions on the primary outcome.

We will check whether the same pattern of outcomes is apparent for patients undergoing lateral nerve root decompression and those undergoing discectomy, and for other subgroups defined by baseline body mass index, baseline HADS score, and single versus multiple anatomic levels of surgery. In addition to the analyses at one year, we will also compare the groups at 6 weeks (beginning of rehabilitation programme in the intervention group) and 3, 6, and 9 months.

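### As described, each main-effect comparison appears to leave out the other randomised factor; estimating both from one model would be a free improvement

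*Protocol article*

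**What the plan says.** The Proposed Analyses section of the protocol article compares groups on one-year ODI by analysis of covariance, "with adjustment for stratifying block using a linear mixed model". It then sets out the factorial comparisons: "Parallel analyses will be performed for booklet vs. no-booklet and rehabilitation vs. no-rehabilitation, with the sample-size calculation given above applying to each of these". A test of interaction between the two interventions comes after these. No covariate other than stratifying block is specified, and the other randomised factor is neither listed as a term nor excluded.

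The calculation referred to is in Trial Sample. It aims "to have a 90% chance of detecting a between-group difference of 8 points on the ODI", with these expected values: "We anticipate a mean ODI of 40 in the control group and 32 in the exercise group at 1 year". On variability it says: "This calculation assumes a standard deviation of 20 in each group". It allows for 23% loss. On numbers: "The trial aims to recruit 344 patients into the trial with 86 patients in each of the 4 sub-groups".

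Three other statements matter. Trial Design balances the four groups within surgeon and procedure at randomisation. Interim analysis states that no interaction is assumed. Proposed Analyses restricts multiple imputation to patients who have some follow-up but no one-year outcome.

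**The concern.** In a 2 × 2 factorial trial, a comparison of the two levels of one factor contains patients at both levels of the other. If the other factor works and is not in the model, its effect is counted as residual variation. The comparison is then less precise than it need be. The statement that one sample-size calculation serves both factors would also depend on which SD the planning value of 20 describes.

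A second issue concerns the patients who are analysed. Randomisation makes the share of booklet recipients the same with and without rehabilitation. Losses can disturb that. A comparison that ignores the booklet would then count part of the booklet effect as a rehabilitation effect, or the reverse. Both factors are primary, so both estimates are exposed.

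**Working it through.** **Inputs.** From Trial Sample: difference 8, SD 20, two-sided alpha 0.05, power 90%, loss 23%, total 344 (172 per side of each factor). Assumption: the other factor is also worth 8 points, because the plan applies the same calculation to both; smaller and larger values are shown below.

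**1. The plan's own figure.** n per side = 2 × (1.960 + 1.282)² × 20² / 8² = 131.3, so 132. Inflating per side, 132 / 0.77 = 171.4, so 172 and a total of 344. Inflating the total, 264 / 0.77 = 342.9, so 343. The stated 344 is reproduced. Evaluable patients: 344 × 0.77 = 264.9, or 132.4 per side. Power is 90.2% (normal) or 90.0% (noncentral t).

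**2. SD 20 read as within-cell.** With the other factor balanced and worth d points, the SD of each side is √(20² + d²/4). For d = 8 this is √(400 + 16) = 20.40. Power of the comparison without the other factor:

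| Effect of other factor (points) | Power, normal | Power, t |
|---|---|---|
| 0 | 90.2% | 90.0% |
| 4 | 89.9% | 89.7% |
| 8 | 89.1% | 88.9% |
| 10 | 88.4% | 88.2% |

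With the other factor in the model, power returns to 90.2% / 90.0%. A simulation for d = 8 (66 per cell, 40,000 runs) gave 89.3% without it and 89.9% with it. Holding 90% without it would take 274 evaluable patients, and 274 / 0.77 gives 356 recruited, 12 more than planned.

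**3. SD 20 read as the SD of each compared group.** The other factor's effect is already inside the 20, so the one-factor comparison has 90.2%. Modelling the other factor reduces the SD to √(400 − 16) = 19.60, and power rises to 91.3% (normal) or 91.1% (t).

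**4. What the covariance adjustment could recover.** The extra variance is 16. A covariate with correlation r to the outcome removes r² × 400, which equals 16 at r = 0.2. That brings the within-cell case back to 90.2%. At r = 0.5 the one-factor comparison has 95.6%. These correlations are assumptions.

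**5. Mixing of effects through loss.** Bias in the rehabilitation effect = 8 × (booklet share among rehabilitation patients − booklet share among the rest), taken over the patients analysed. The loss patterns below are assumptions; the article gives only 23% overall, and each pattern averages 23%. The order is usual care / booklet only / rehabilitation only / both, and no imputation is applied.

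| Loss (%) | Booklet share, rehabilitation vs none | Bias (points) |
|---|---|---|
| 23/23/23/23 | 50% vs 50% | 0 |
| 28/28/18/18 (one factor only) | 50% vs 50% | 0 |
| 33/23/23/13 (roughly additive) | 87/164 = 53.0% vs 77/144 = 53.5% | 0.03 |
| 35/19/19/19 | 81/162 = 50% vs 81/146 = 55.5% | 0.44, benefit understated |
| 28/18/18/28 (crossed) | 72/154 = 46.8% vs 82/154 = 53.2% | 0.52, benefit understated |
| 15/31/31/15 (crossed) | 85/154 = 55.2% vs 69/154 = 44.8% | 0.83, benefit overstated |
| 33/13/13/33 (extreme crossed) | 67/154 = 43.5% vs 87/154 = 56.5% | 1.04, benefit understated |

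Bias arises only when the booklet share differs between the two sides. Unequal loss alone is not enough.

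**The case against.** The strongest reply is that the omission is inferred from silence. An article need not list every model term, and an analysis plan that is not shown may already fit both factors. That stands as a caution. Even so, the structure given (parallel two-level comparisons, one named adjustment, interaction afterwards) would lead an analyst working from the article to fit two one-factor models.

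A reader might go further and infer that the trial is too small or that the stated 90% power is missed. The documents do not support this. In Trial Sample the SD is given directly after the control and exercise means, where the word group most naturally means the two sides compared, and on that reading 90% is met. The usage elsewhere is mixed, so neither reading is certain. The unadjusted calculation also leaves out any gain from the planned covariance and stratum adjustment, and variation of about 4% (16 / 416) would cancel the shortfall.

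A reader might also infer that unequal loss as such biases the results. It does not: loss driven by one factor gives no bias and roughly additive loss almost none. The larger figures need crossed loss, for which the article gives no mechanism. Higher loss in the usual-care group alone is more plausible, because patients learn their allocation after surgery and that group receives neither intervention. The planned imputation would reduce the bias but does not cover patients with no follow-up.

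**Conclusion.** The point holds as a modest improvement in analysis, not as an error in the sample size. On the natural reading, each primary comparison omits the other randomised factor. The cost in power is about 1 percentage point or less if the other factor's effect is no more than 8 points. It takes power below 90% only if SD 20 is within-cell, the other factor has a real effect, and neither covariates nor strata explain any variance. Possible mixing of the two effects runs from 0 to about 1 of the 8 target points before imputation, under loss patterns that are assumed. A joint main-effects model matches the no-interaction assumption in Interim analysis, and under that assumption it removes the mixing. If the other factor works at the planned size, the joint model is the more precise under either reading of the SD.

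**What to change.** Replace the two parallel comparisons with one primary linear mixed model for one-year ODI. It should contain the rehabilitation indicator, the booklet indicator, the planned covariate or covariates of the analysis of covariance, and the stratification term. Read both main effects from it, then add the product term to the same model for the interaction test. It would also help to state whether the SD of 20 is within-cell or the SD of each compared group.

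The cost is a sentence or two and one degree of freedom, with no new data or patients. If losses were crossed, the two indicators would become slightly correlated. In the most extreme pattern above the correlation is (67² − 87²) / 154² = −0.13, which raises the variance of each estimate by a factor of 1 / (1 − 0.13²) = 1.017. That is less than the ratio 416 / 400 = 1.04 gained when the other factor is worth 8 points.

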### Outcome measures

The primary outcome measure is the Oswestry Disability Index (ODI, version 2.1), a disease-specific patient-completed questionnaire documenting function[56] of known validity and reliability [57], measured at the one year follow-up visit. This will be complemented by a series of secondary outcome measures. At baseline (the pre-operative assessment) and each follow-up point, simple 10 cm visual analogue scales (VAS) will be used to record least and usual back and leg pain, from which average values will be derived [58]. Measures of patient satisfaction will focus on the patient's satisfaction with the actual procedure undertaken and its outcome as opposed to satisfaction with the hospital's facilities, staff, etc. This will be assessed directly using a 5 point Likert scale ranging from 'complete improvement' to 'significant deterioration', and indirectly by comparing actual outcome with expected outcome. Expected outcome for pain and function will be assessed pre-operatively and at 6 weeks post-operation using 10 cm VAS, with subsequent satisfaction relating to each of these measures being assessed using similar VAS ranging from 'completely satisfied' to 'completely dissatisfied'[19]. Participants in the trial will be asked to complete the HADS [59], a well validated instrument for the assessment of anxiety and depression among patients in non-psychiatric hospital clinics at each assessment point. This will allow us to take pre-operative psychological status into account as a factor potentially affecting the outcome of surgery. In similar fashion, we will use the physical activity component of the Fear Avoidance Beliefs Questionnaire developed by Waddell et al[55] to take perceptions and expectations into account as possible influences on functional outcome. Information will also be collected on the timing and extent of any return to work, plus the nature of the participant's occupation, and on the timing and nature of any re-operations.

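### Baseline BMI and HADS score are to be checked as subgroups; continuous interaction terms would keep more information if the effect changes roughly linearly with the score

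*Protocol article*

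**What the plan says.** Under Proposed Analyses, after the two main comparisons and the test of interaction between the interventions, the article says: "We will check whether the same pattern of outcomes is apparent for patients undergoing lateral nerve root decompression and those undergoing discectomy". It extends this to "other subgroups defined by baseline body mass index, baseline HADS score, and single versus multiple anatomic levels of surgery".

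Four factors are therefore treated alike. Procedure and number of levels are categories by nature; BMI and HADS score are numbers. The article gives no cut-points, number of groups or model for them, and plans neither as a continuous modifier. The only interaction test it names is between rehabilitation and booklet.

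Both scores should be available for the purpose. On HADS, Outcome measures says "Participants in the trial will be asked to complete the HADS", at every assessment point. BMI is in the list of pre-surgery characteristics under Proposed Analyses: "This will include age, sex, type of surgery, ethnic background, marital status, body mass index, occupation type, work status and smoking status". Trial Sample confirms the timing: "Written informed consent will be obtained from all patients and baseline assessment completed prior to surgery and randomisation into the trial".

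**The concern.** A subgroup made from a numeric score treats everyone on one side of a cut as alike and neighbours across it as different. If the effect of rehabilitation or the booklet rises or falls steadily with BMI or HADS, this discards information that a model using the score would keep, and the answer partly depends on where the cut falls. The trial is sized for main effects, so its power to show who benefits is limited to begin with. The stake is a secondary one: a real gradient in effect may be missed, or may be described only as a contrast between two arbitrary groups.

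**Working it through.** **1. The plan's own figure.** Inputs from Trial Sample: difference 8 ODI points, SD 20, power 90%, two-sided alpha 0.05, loss 23%.

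- Per group: 2 × [20 × (1.960 + 1.282)/8]² = 131.3, rounded up to 132; total 264.
- Allowing for loss: 264/0.77 = 342.9, so 343. The article states 344, which is 4 × 86. It reproduces and is not in dispute.
- Expected number analysed: 344 × 0.77 = 264.9, about 265.

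**2. Information kept after cutting a score.** Assume a normal score and an effect that changes linearly with it. The information kept, relative to a linear term, is the squared correlation between the score and its category scores. For two groups cut at quantile p this is e = φ(z_p)²/[p(1 − p)]. At the median, e = 0.3989²/0.25 = 2/π = 0.637.

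To express this as power, take a gradient that a linear term detects with 80% power. Its noncentrality is (1.960 + 0.842)² = 7.85. After categorising it is 7.85 × e, referred to a chi-square with the relevant degrees of freedom. With 1 df, power is about Φ(√(7.85e) − 1.96).

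| Form of the score | Information kept | Lost | Power |
|---|---|---|---|
| Linear term | 100% | 0% | 80% |
| Two groups, 50/50 | 63.7% | 36% | 61% |
| Two groups, 40/60 | 62.2% | 38% | 60% |
| Two groups, 30/70 | 57.6% | 42% | 57% |
| Two groups, 20/80 | 49.0% | 51% | 50% |
| Two groups, 10/90 | 34.2% | 66% | 37% |
| Thirds, scored as a trend | 79.3% | 21% | 70% |
| Quarters, scored as a trend | 86.1% | 14% | 74% |
| Fifths, scored as a trend | 89.7% | 10% | 76% |
| Thirds, unordered (2 df) | 79.3% | 21% | 60% |
| Quarters, unordered (3 df) | 86.1% | 14% | 57% |

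Unordered groups keep more information than a median split but spend it over extra degrees of freedom, so their power is no better. A simulation with 265 patients and SD 20 (4,000 runs) gave 78% for the linear term and 60% for the median split, close to the 80% and 61% above.

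Normality matters. With right-skewed scores (gamma, skewness 0.4 to 2) a median split loses about 37% to 52%.

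**3. On the ODI scale for this trial.** Use 265 analysed, half per level of each factor, and SD 20.

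- Linear interaction: SE = 2 × 20/√265 = 2.457 points per SD of the score. Detectable with 80% power: 2.802 × 2.457 = 6.9 points per SD.
- Median split: the halves differ by 2√(2/π) = 1.596 SD in mean score, and the contrast has SE = 4 × 20/√265 = 4.914. Detectable with 80% power: 6.88/√0.637 = 8.6 points per SD. Equivalently, 265 patients do the work of 265 × 0.637 = 169.

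The documents give no size for any gradient, so these values are assumptions:

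| Assumed change in effect per SD | Linear term | Median split |
|---|---|---|
| 2 points | 13% | 10% |
| 4 points | 37% | 25% |
| 5 points | 53% | 37% |
| 6 points | 69% | 50% |

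**The case against.** The article gives these checks half a sentence. It says which factors will be examined, not how each enters a model, and a condensed article may leave that to a full protocol or analysis plan. This stands in part: absent cut-points are not a finding, and categories might be meant only for display. But subgroups defined by a score, listed beside two true categories, are most naturally read as cut scores, and nothing in the article points the other way.

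Three stronger readings are tempting and are not supported.

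- A reader might infer that the plan discards about a third of the information. That needs a single cut near the median, a roughly normal score and a linear gradient. The article states none of these, and the loss could be clearly smaller or larger.
- A reader might infer that categories bring no gain. They avoid imposing a straight line, and for a threshold-type effect they can do better than a linear term.
- A reader might take the remark under Outcome measures that HADS lets the trial "take pre-operative psychological status into account as a factor potentially affecting the outcome of surgery" as a plan to study effect modification. It describes a prognostic role and says nothing about whether the interventions work differently by HADS.

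The size of the practical difference is also open. A gradient of 5 points per SD is steep beside a planned effect of 8 points: since 8/5 = 1.6, the effect would run from 0 to 16 points between 1.6 SD either side of the mean. At 2 points per SD neither method has useful power, and the choice hardly matters.

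**Conclusion.** The point holds as a minor, conditional one. Read naturally, the plan cuts two numeric baseline scores to look for variation in effect. If the score is roughly normal and the gradient linear, any two-way cut loses at least about 36% of the information on that gradient, and 42% to 66% for cuts from 30/70 to 10/90. Three to five ordered groups scored as a trend lose about 21% to 10%. Unordered thirds or quarters have about 60% or 57% power where a linear term has 80%. The ODI-scale figures further assume 265 analysed and a residual SD of 20, with no gain from baseline adjustment.

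These are secondary checks. The primary comparison at one year, the sample size and the test of interaction between the interventions are untouched.

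**What to change.** Reword the subgroup sentence so that variation by baseline BMI and baseline HADS score is tested by adding, for each factor, an intervention-by-continuous-score interaction to the primary model, with the score's main effect included. Report the estimated effect with its confidence interval at low, middle and high values of the score, and use categories for display only. Procedure and number of levels stay as categories.

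The cost is analysis wording; no further data or patients are needed. The downside is the assumed linear trend, which would serve a threshold-type effect less well, so add one curvature term as a check and report it alongside.

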### Interim analysis

As active rehabilitation may potentially produce a worse outcome, there will be an interim analysis once a third of the target number of patients have reached 6 month follow-up, this would allow for 60 patients per group for the main effect of each factor. At this analysis, an independent Data Monitoring Committee (DMC) will apply stopping rules of p < 0.01 for harm, and p < 0.001 for benefit associated with each intervention. We are assuming that there is no interaction between the rehabilitation and booklet however we have requested that the DMC inform us if it becomes apparent that this is not the case. If the DMC recommend stopping recruitment to one of the trial factors only, recruitment and randomisation regarding the other factor will continue but the intervention to which the stopping rule has been applied will be applied (or withheld) for all patients subsequently randomised. For example, if an interim analysis demonstrates a significant beneficial effect of rehabilitation (based on the pre-specified stopping rules), then both the non rehab groups i.e. no rehab no book, book only will be stopped and the remaining trial population will be randomised to either the rehabilitation only or rehabilitation and booklet group.

